### Patient replacement and handling of missing data

Patients not fulfilling eligibility criteria resulting in the exclusion of the ITT analysis will be replaced. If outcome data cannot be obtained by a study follow-up visit at the outpatient clinic, the patient will be contacted by telephone to gather primary and most secondary outcome data. The postoperative ultrasound of these patients and all data on patients that cannot be contacted will be considered missing. For missing data, a multiple (% of missing data) imputation approach will be selected and justified at the time of analysis, based on the observed missing data pattern and using relevant patient characteristics and outcome predictors. The imputed values will be primarily estimated within the observed data ranges. We will not impute missing values if the percentage missing is below 2. If the missing data appear not missing at random, a worse- and best-case scenario will be run, in which all patients lost to follow-up in the placebo arm are considered free of symptomatic gallstone disease, and all patients lost to follow-up in the UDCA arm are considered not free of symptomatic gallstone disease, and vice versa. Missing values of baseline characteristics will not be imputed. Mixed effects modelling will be applied for the analysis of repeated measures from questionnaire data, thereby simultaneously accounting for missing data.

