### Assessment and analysis of primary outcome

The primary outcome is the proportion of patients with symptomatic gallstone disease within 24 months of follow-up. Symptomatic gallstone disease is defined as a biliary disease (biliary pancreatitis, acute cholecystitis, choledocholithiasis, cholangitis or biliary colics) for which a hospital visit or admission was required. To assess the primary outcome, follow-up appointments are held at 6 and 16 weeks, and 6, 12 and 24 months by one of the blinded investigators. All primary endpoints will be reviewed by a blinded independent endpoint adjudication committee.

To provide an estimator of the effectiveness of UDCA, we will perform a standard ITT analysis. The difference between outcomes by study arm will be compared using the chi-squared test with a risk ratio (unless editors of the accepting journal suggest to report odds ratio) as an indicator for effect size, as shown in Table 2. The results of the mITT and other data sets will be provided in a supplementary appendix, if no contradictory findings are to be reported.

**Table 2 Tab2:** Gallstone-related outcomes

	UDCA (***n***=)	Placebo (***n***=)	Effect size	***p***
*Primary outcome*				
**Symptomatic gallstone disease**—*n* (% *n*/*N*)				
Biliary pancreatitis				
Acute cholecystitis				
Choledocholithiasis				
Cholangitis				
Biliary colic				
*Secondary outcomes*				
**Presence of gallstones/sludge on ultrasound at 24 months**—*n* (% *n*/*N*)				
**Newly formed gallstones/sludge on ultrasound at 24 months**—*n* (% *n*/*N*)				
**Cholecystectomy**—*n* (% *n*/*N*)				

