We are aware that many studies have reported poor compliance of UDCA after bariatric surgery. Consequently, there is a chance that the expected attrition rate will be exceeded. If this is the case, we assume that we will not need a higher number of patients to assure the availability of sufficient evaluable patients, because the relative reduction is probably larger than the 50% reduction used in the power analysis.

In our trial, the postoperative ultrasound is performed during a regular follow-up visit at the outpatient clinic. Due to the unforeseen and unique bankruptcy of two participating centres, and the coronavirus disease (COVID-19) pandemic, the regular follow-up schedule was suspended temporarily. Therefore, we decided to maintain a relatively large window (18 to 30 months) in which the postoperative ultrasound—originally scheduled at 24 months—has to be carried out. We will explore whether the contrast between the two study arms is stable across different time frames in order to assess the impact of the logistic artefact.

The results of the UPGRADE trial will optimise the postoperative management of bariatric patients and probably lead to a reduction of patients with symptomatic gallstone disease. This trial has the potential to affect daily clinical practice and improve patient outcomes. Second, cost-effectiveness, cost-utility and budget impact analyses of postoperative UDCA prophylaxis may demonstrate the societal value of prophylactic UDCA treatment for health care providers, insurers and taxpayers.

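### The worst/best-case analysis of the primary outcome depends on a condition the data cannot establish; it should be run whenever a primary outcome is missing, with recorded events protected

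*SAP article*

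**What the plan says.** All of the missing-data rules stand under the heading Patient replacement and handling of missing data in the SAP article:

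- A patient who misses the clinic visit is telephoned. If that fails, "all data on patients that cannot be contacted will be considered missing".
- The default is multiple imputation, where the "imputation approach will be selected and justified at the time of analysis, based on the observed missing data pattern".
- There is a lower limit: "We will not impute missing values if the percentage missing is below 2".
- The extreme scenarios are conditional: "If the missing data appear not missing at random, a worse- and best-case scenario will be run". In one scenario "all patients lost to follow-up in the placebo arm are considered free of symptomatic gallstone disease" and every lost UDCA patient is given the event; in the other the roles are reversed.

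Under Assessment and analysis of primary outcome: "The primary outcome is the proportion of patients with symptomatic gallstone disease within 24 months of follow-up". Events can come to light well before month 24, since "follow-up appointments are held at 6 and 16 weeks, and 6, 12 and 24 months".

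The section Additional analyses adds the mITT set, two full analysis sets, two per-protocol sets, a compliance-adjusted logistic regression and interaction terms. Each changes the population or the model. None changes what is assumed about a missing primary outcome.

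**The concern.** Missing not at random means that, given everything observed, the chance of being missing still depends on the unseen value. The observed data are compatible with that and equally compatible with missing at random. A pattern can suggest informative loss, for instance more loss in one arm or in one risk group. But such a pattern may be fully explained by observed variables, and its absence does not exclude informative loss. The word *appear* therefore hands the decision to the analyst, without a criterion, at the time of analysis.

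The consequence is limited but real. The primary outcome is uncommon: the Abstract puts it at about 8–15% over 24 months. A few lost patients can then be a sizeable fraction of the events. If the condition is judged not to be met, the primary paper would carry no planned analysis showing how the result responds to the missing outcomes.

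A smaller problem sits beside it. The outcome is cumulative, so an event recorded at, say, month 10 settles it. Neither the clause on uncontactable patients nor the scenario rule on patients lost to follow-up exempts someone whose event is already on record.

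**Working it through.** **No figure to reproduce.** The document gives no loss rate, sample size or power and refers to the protocol for the sample size. What follows is illustration.

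**Inputs from the document.** Background risk 8–15% (Abstract); 50% relative reduction (Discussion); two-sided 0.05 (General principles); 1:1 allocation (Summary study protocol); chi-squared test with risk ratio (Assessment and analysis of primary outcome).

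**Assumptions.** Placebo risk p0 = 0.10, so p1 = 0.05; equal loss L per arm; no recorded events among the lost.

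**Step 1: can the data trigger the rule?** Suppose 10% of UDCA patients are lost, the observed UDCA risk is 4% and the placebo risk is 8%. Let q be the true risk among the lost UDCA patients:

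- q = 4%: (0.9 × 0.04 + 0.1 × 0.04) / 0.08 = 0.040 / 0.08 = 0.50
- q = 8%: (0.036 + 0.008) / 0.08 = 0.044 / 0.08 = 0.55
- q = 16%: (0.036 + 0.016) / 0.08 = 0.052 / 0.08 = 0.65

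The observed data are the same in all three cases, but the true risk ratio is not. No inspection of the data could decide whether to run the scenarios.

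**Step 2: the bounds.**

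Worst RR = [p1(1 − L) + L] / [p0(1 − L)]

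Best RR = p1(1 − L) / [p0(1 − L) + L]

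| L | Worst | Best |
|---|---|---|
| 2% | (0.049 + 0.02) / 0.098 = 0.70 | 0.049 / (0.098 + 0.02) = 0.42 |
| 5% | (0.0475 + 0.05) / 0.095 = 1.03 | 0.0475 / (0.095 + 0.05) = 0.33 |
| 10% | (0.045 + 0.10) / 0.090 = 1.61 | 0.045 / (0.090 + 0.10) = 0.24 |

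The worst case reaches RR = 1 when L / (1 − L) = p0 − p1 = 0.05, that is L = 0.05 / 1.05 = 4.8%.

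**Step 3: significance, at an assumed 80% power.** Pooled-variance formula:

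n = [1.96 × √(2 × 0.075 × 0.925) + 0.8416 × √(0.09 + 0.0475)]² / 0.05² = (0.7301 + 0.3121)² / 0.0025 ≈ 434.4, so 435 per arm.

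Uncorrected chi-squared test with whole-number counts (hence small differences from step 2):

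| Loss per arm | Complete-case RR (p) | Worst-case RR (p) | Best-case RR |
|---|---|---|---|
| 9 (2%) | 21/43 = 0.49 (0.004) | 30/43 = 0.70 (0.11) | 21/52 = 0.40 |
| 22 (5%) | 21/41 = 0.51 (0.008) | 43/41 = 1.05 (0.82) | 21/63 = 0.33 |
| 44 (10%) | 20/39 = 0.51 (0.010) | 64/39 = 1.64 (0.009, against UDCA) | 20/83 = 0.24 |

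The ratios are ratios of event counts, since the two arms have equal denominators.

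**Step 4: range.** Eight settings were tried: placebo risk 8, 10, 12 or 15%, each at 80% and 90% power. At 5% loss the worst-case RR runs from 0.85 to 1.17 and is never significant. At 2% loss it is non-significant in seven of the eight. At 1% loss, below the imputation threshold, it is non-significant in one (8% risk, 553 per arm: RR 28/44 = 0.64, p = 0.051). Falling below the threshold does not by itself make the check unnecessary.

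**The case against.** The strongest reply has four parts.

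*The bounds are extreme.* The worst case gives every lost UDCA patient an event and every lost placebo patient none, against a background risk of 8–15%. This stands. The figures above do not show that the trial's result is fragile, and the three-value example in step 1 moves the risk ratio only from 0.50 to 0.65 at 10% loss in one arm. That is an argument for graded assumptions alongside the bounds, not for leaving the check to judgement.

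*Readers can compute the bounds themselves.* The plan promises losses by arm, a CONSORT flow diagram and n/N in Table 2. This partly stands: the condition governs what the authors present, not whether fragility could ever be seen. But a count of losses equals a count of missing outcomes only if nobody had an event before being lost.

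*Recorded events are surely kept.* A reader might infer from the literal wording that known events will be thrown away. The document does not support that. The clause follows a sequence of clinic visit, then telephone call, and most naturally means what could not be obtained at that contact. The mITT definition drops only patients without any measurement after randomisation, all primary endpoints go to adjudication, and the Kaplan-Meier analysis of time to symptomatic disease needs dated events up to loss. What stands is an ambiguity that one sentence would remove.

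*The imputation model may be chosen blind.* A reader might infer that it is selected after unblinding. General principles sets the earliest moment for breaking the code but does not say on which side of it the model is chosen, and a missing-data pattern can be examined blinded. Only the silence on the order can be criticised.

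A reader might also take the sentence beginning "Due to the unforeseen and unique bankruptcy of two participating centres" to mean that centre drives loss of the primary outcome. The Discussion links it, with the pandemic, to a temporary suspension of the visit schedule and to the ultrasound window. It does not mention lost primary outcomes, for which telephone follow-up is planned. The list of imputation covariates is detail an article may leave out.

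**Conclusion.** The point holds for the condition. The plan's only check on the missing-outcome assumption is tied to a judgement that observed data cannot settle, so it may never be run. This should be changed, and confidence in it is high. The protection of recorded events is a clarification: the wording leaves a gap, although the rest of the document suggests the intended reading. Fixing the imputation model before code break is sensible but secondary.

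On size, with a placebo risk of 10%, RR 0.50 and equal loss per arm, the bounds include no effect once loss reaches about 4.8%, and significance can go earlier. All loss rates, sample sizes and power values are assumptions; only the risk range, the 50% reduction, the significance level and the allocation ratio come from the document. If actual loss proves very small, the practical effect will be small too, and the unconditional analysis would show this.

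**What to change.** Amend the missing-data section as follows.

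1. Delete the condition. Report the worst-case and best-case pair, already defined there, whenever any primary outcome is missing, including when less than 2% is missing and nothing is imputed.
2. Preferably add graded assumptions between the extremes, for example a rising event risk among lost UDCA patients, so that readers can see how far the assumption must move before the conclusion changes.
3. In the same sentence, state that an event recorded before loss counts as an event in every analysis, and that only patients event-free at last contact are treated as missing.
4. As a secondary step, state that the imputation model is fixed before the randomisation code is broken.

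The cost is a few lines of text and two supplementary runs, plus a short table if the graded analysis is added. Design and data collection are unaffected. The drawback is that the extremes may look unfavourable and must be shown, so they should be labelled as bounds.

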### Baseline characteristics

The following characteristics of patients will be shown per treatment arm in a baseline table (Table 1): age (years), sex (% F), ethnicity, weight at baseline and at time of surgery (kg), body mass index (BMI) (kg/m^2^) at baseline, hypertension (% yes), dyslipidaemia (% yes), type 2 diabetes (% yes), pain syndrome (% yes), history of abdominal surgery (% yes), medication prior to surgery (% statins, birth control pills, oestrogens), preoperative cholecystolithiasis (% yes), type of surgery (% RYGB), baseline health utility score (derived from the EuroQol 5 Dimensions 5 Level (EQ-5D-5L) questionnaire and the corresponding Dutch scoring algorithm for observed health status profiles) [8]. Categorical variables will be summarised as the proportion of patients with the count divided by the total number of evaluated patients. Continuous variables with a normal distribution will be summarised using means and standard deviations, whereas medians and interquartile ranges will be used in case of non-normal distributions. For continuous variables, a footnote will be added to show the number of evaluated patients. Differences between the study arms will be analysed using the chi-squared test, independent *t* test or Mann-Whitney test and reported at the discretion of the publishing journal’s policy regarding significance testing in baseline tables for RCTs.

**Table 1 Tab1:** Baseline characteristics

	UDCA (***n***=)	Placebo (***n***=)
**Age**—years, mean (SD)		
**Sex**—F, *n* (% *n*/*N*)		
**Ethnicity**		
Dutch		
Surinamese		
Dutch Caribbean		
Moroccan		
Turkish		
Others		
**Baseline weight**—kg		
**Baseline BMI**—kg/m^2^		
**Hypertension**—yes, *n* (% *n*/*N*)		
**Dyslipidaemia**—yes, *n* (% *n*/*N*)		
**Type 2 diabetes**—yes, *n* (% *n*/*N*)		
**Pain syndrome**—yes, *n* (% *n*/*N*)		
**History of abdominal surgery**—yes, *n* (% *n*/*N*)		
**Medication prior to surgery**—yes, *n* (% *n*/*N*)		
Statins		
Birth control pills		
Oestrogen		
**Preoperative cholecystolithiasis**—yes, *n* (% *n*/*N*)		
**Type of surgery**—RYGB, *n* (% *n*/*N*)		
**Baseline health utility score**—*n*, mean (SD)		

### Assessment and analysis of primary outcome

The primary outcome is the proportion of patients with symptomatic gallstone disease within 24 months of follow-up. Symptomatic gallstone disease is defined as a biliary disease (biliary pancreatitis, acute cholecystitis, choledocholithiasis, cholangitis or biliary colics) for which a hospital visit or admission was required. To assess the primary outcome, follow-up appointments are held at 6 and 16 weeks, and 6, 12 and 24 months by one of the blinded investigators. All primary endpoints will be reviewed by a blinded independent endpoint adjudication committee.

To provide an estimator of the effectiveness of UDCA, we will perform a standard ITT analysis. The difference between outcomes by study arm will be compared using the chi-squared test with a risk ratio (unless editors of the accepting journal suggest to report odds ratio) as an indicator for effect size, as shown in Table 2. The results of the mITT and other data sets will be provided in a supplementary appendix, if no contradictory findings are to be reported.

**Table 2 Tab2:** Gallstone-related outcomes

	UDCA (***n***=)	Placebo (***n***=)	Effect size	***p***
*Primary outcome*				
**Symptomatic gallstone disease**—*n* (% *n*/*N*)				
Biliary pancreatitis				
Acute cholecystitis				
Choledocholithiasis				
Cholangitis				
Biliary colic				
*Secondary outcomes*				
**Presence of gallstones/sludge on ultrasound at 24 months**—*n* (% *n*/*N*)				
**Newly formed gallstones/sludge on ultrasound at 24 months**—*n* (% *n*/*N*)				
**Cholecystectomy**—*n* (% *n*/*N*)				

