**Results:**

The primary endpoint of this trial is symptomatic gallstone disease within 24 months after bariatric surgery, defined as admission or hospital visit for symptomatic gallstone disease. Secondary outcomes consist of the development of gallstones/sludge on ultrasound at 24 months in the gallstone-negative group at baseline, presence of gallstones/sludge on ultrasound at 24 months, number of cholecystectomies, side effects of UDCA, therapy compliance, quality of life, costs and revenues. Analyses will be completed according to this pre-specified SAP. The main analysis will be performed as a standard ITT analysis using the chi-squared test.

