## Summary study protocol

The UPGRADE trial is a randomised, placebo-controlled, double-blind multicentre trial comparing the prophylactic use of UDCA versus placebo in patients with morbid obesity undergoing bariatric surgery. Patients with an intact gallbladder and scheduled to undergo Roux-en-Y gastric bypass (RYGB) or sleeve gastrectomy (SG) were included. Patients were excluded in case of the existence of symptomatic gallstone disease prior to bariatric surgery, prior bariatric surgery, prior gallbladder surgery, inflammatory bowel disease and other conditions of the small intestine and liver which may interfere with enterohepatic circulation of bile salts, hypersensitivity to ingredients of UDCA or placebo, and intake of UDCA within the last 30 days before screening. Patients were randomly assigned to either UDCA 900 mg daily for 6 months or placebo in a 1:1 ratio. Randomisation was done prior to surgery with an online computer software program (ALEA AMC, Amsterdam, the Netherlands, version 2.2) and implemented into a web-based application. Randomisation was stratified for the presence of gallstones (yes versus no) and type of surgery (RYGB versus SG) and performed by using random block sizes of 4, 6 and 8. Data are collected during hospitalisation and study visits at 6 weeks (window 4–8 weeks) and 16 weeks (window 14–18 weeks) and at 6 months (window 5–9 months), 12 months (window 10–15 months) and 24 months (window 24–30 months) by standardised case report forms. Questionnaires are gathered at baseline, 6 weeks, and 3, 6, 12, 18 and 24 months (windows 1 week before to 2 weeks after the date of administration). The primary outcome is symptomatic gallstone disease within 24 months, defined as admission or hospital visit for symptomatic gallstone disease. Secondary outcomes consist of the development of gallstones/sludge on ultrasound at 24 months in the gallstone-negative group at baseline (window 18–30 months), presence of gallstones/sludge on ultrasound at 24 months (window 18–30 months), number of cholecystectomies, time to symptomatic gallstone disease and cholecystectomy, side effects of UDCA, therapy compliance, quality of life, costs and revenues. Safety outcomes are adverse events (AEs), serious adverse events (SAEs) and suspected unexpected serious adverse reactions (SUSARs). For the sample size calculation, we refer to the study protocol [4]. On 22 October 2018, all included patients underwent surgery, and complete 2-year follow-up data are expected in November 2020. For the complete study protocol, we refer to the previous publication [4].

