## Statistical analysis plan

### General principles

The randomisation code will not be broken until the last patient reaches 24 months of follow-up, all primary endpoints are reviewed by a blinded independent endpoint adjudication committee, and data cleaning is completed. The analyses will be performed after data verification and validation have been carried out and after this SAP has been accepted for publication. Analyses will be done by the investigators and biostatistician of the UPGRADE study group, using the most recent version of the SPSS statistical software at the time of analysis. All statistical tests will use a two-sided *p* value of 0.05, and two-sided 95% confidence intervals will be presented for all estimates.

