### Additional analyses

Besides the IIT, we will perform a mITT. In case of lack of compliance or improper conduct of a trial, the inclusion of all the data in the IIT or mITT tends to reduce the effectiveness in a clinical trial since the groups to be compared may look more similar [9]. Therefore, we will also use two alternative FASs of patients to further explore treatment effectiveness—as the FAS might be more appropriate to predict effectiveness in the real world. In addition, to estimate efficacy, we will perform a standard analysis with the two PPSs of patients. However, the effect of compliers assigned to UDCA should be somehow compared with the effect of compliers assigned to placebo, excluding compliers on placebo who would not have been compliant on UDCA, as proposed by Rozenkranz [9]. Therefore, both analyses with the PPSs will be repeated with an exploratory logistic regression on having symptomatic gallstone disease taking into account predicted UDCA compliance in the placebo arm. The results of the above-mentioned data sets will be provided in a supplementary appendix, and any differences between the analyses will be subject of discussion and interpretation.

Stratified randomisation by the presence of gallstone disease at baseline and type of surgery was done to prevent bias while estimating the treatment effect of UDCA on symptomatic gallstone disease. An exploratory logistic regression with interaction terms of treatment with each of the stratification factors will be performed to see if UDCA outcomes may differ by subgroup.

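### The primary chi-squared test and crude risk ratio ignore the randomisation strata; if baseline gallstones predict the outcome, the result is mildly conservative and a little precision is lost

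*SAP article*

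**What the plan says.** **Design.** Under Summary study protocol: "Randomisation was stratified for the presence of gallstones (yes versus no) and type of surgery (RYGB versus SG) and performed by using random block sizes", with 1:1 allocation.

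**Primary analysis.** The abstract states: "The main analysis will be performed as a standard ITT analysis using the chi-squared test". Assessment and analysis of primary outcome repeats this: "The difference between outcomes by study arm will be compared using the chi-squared test with a risk ratio". The risk ratio is to be shown "unless editors of the accepting journal suggest to report odds ratio". General principles sets the level: "All statistical tests will use a two-sided *p* value of 0.05, and two-sided 95% confidence intervals will be presented for all estimates".

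**Use of the strata.** They appear in one analysis only, under Additional analyses: "An exploratory logistic regression with interaction terms of treatment with each of the stratification factors will be performed". No stratified or adjusted estimate of the main effect is planned, even as a sensitivity analysis.

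**Secondary outcomes.** Cholecystectomy and both ultrasound outcomes are also compared by a plain chi-squared test.

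**Prognostic value of the strata.** The Discussion expects roughly one patient in five to have asymptomatic gallstones and treats a higher risk in them as a possibility. For the two operations it reports similar rates of gallstone disease.

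**The concern.** Stratified blocks force the arms to be nearly equal in the share of patients with gallstones. If gallstones predict the outcome, this removes one source of chance difference between the arms. The pooled chi-squared test and the crude risk-ratio interval still count that source as noise. Their standard error is then larger than the real sampling error. The p value is somewhat too large, the interval somewhat too wide, and some of the precision gained by stratifying is not used.

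This matters a little more here because the Discussion accepts that attrition may exceed expectation, while the sample size stays as it was.

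A linked, smaller point is that the clause on editors leaves the primary effect measure open to change after the result is known.

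**Working it through.** **Inputs from the SAP article**
- Two-sided alpha 0.05; 1:1 allocation; random blocks of 4, 6 and 8 within strata.
- Control event rate 8–15% by 24 months (Introduction). The rate used for the power calculation is not given.
- A 50% relative reduction (Discussion).
- Gallstone prevalence about 20% (Discussion).

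**Assumptions, because the article gives no figure**
- Gallstone risk ratio R (gallstones v none): 1 to 6.
- Surgery type: not prognostic, 10% sleeve gastrectomy.
- Sample size: not stated in the article, so set to give 80% power. The pooled-variance formula for two proportions gives N = 1106, 748 and 556 at control rates 8%, 11.5% and 15%.

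With no stated N or power to reproduce, the figure to check is the nominal alpha of 0.05.

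**Step 1: analytic check under no treatment effect**

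With overall risk p, the risk without gallstones is b = p / (0.8 + 0.2R), and with gallstones it is Rb. Then

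r = [0.8·b(1−b) + 0.2·Rb(1−Rb)] / [p(1−p)]

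actual alpha = 2·[1 − Φ(1.96/√r)]

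Example, p = 0.115 and R = 4:
- b = 0.115/1.6 = 0.0719; Rb = 0.2875.
- Within-stratum variance = 0.8 × 0.0719 × 0.9281 + 0.2 × 0.2875 × 0.7125 = 0.0943.
- Total variance = 0.115 × 0.885 = 0.1018.
- r = 0.927; 1.96/√0.927 = 2.036; alpha = 0.042.

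**Step 2: simulated type I error of the crude test** (stratified blocks, 100,000 runs per scenario)

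| Gallstone risk ratio | Control 8% | 11.5% | 15% |
|---|---|---|---|
| 1 | 0.051 | 0.050 | 0.051 |
| 2 | 0.049 | 0.049 | 0.048 |
| 3 | 0.046 | 0.044 | 0.045 |
| 4 | 0.044 | 0.042 | 0.040 |
| 6 | 0.040 | 0.036 | 0.031 |

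The Cochran-Mantel-Haenszel (CMH) test gave 0.049–0.051 throughout. The worked example (0.042) agrees with its cell.

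**Step 3: power under a halved risk, crude → CMH**

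| Gallstone risk ratio | Control 8% | 11.5% | 15% |
|---|---|---|---|
| 3 | 0.811 → 0.815 | 0.812 → 0.820 | 0.815 → 0.826 |
| 4 | 0.815 → 0.823 | 0.815 → 0.828 | 0.818 → 0.838 |
| 6 | 0.819 → 0.834 | 0.820 → 0.844 | 0.823 → 0.856 |

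The loss is 0.4–1.0 points at risk ratio 3, 0.9–2.0 at 4 and 1.6–3.4 at 6. At 2 it is at most 0.4, and at 1 it is nil.

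**Step 4: interval width under a halved risk** (200,000 runs, arms equal within each gallstone stratum)

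The crude risk-ratio interval is wider than the Mantel-Haenszel interval by 0.9–1.9% (risk ratio 3), 1.6–3.3% (4) and 2.9–6.1% (6). Crude coverage at risk ratios 3–6 is about 0.956–0.965, against 0.953–0.954 when stratified.

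**The case against.** The strongest reply is that nothing here is invalid. Any error is conservative, no false positive can come from it, and the plan itself offers no evidence that gallstones are prognostic. It says only that a higher risk is possible, and by its own account surgery type adds little. All of this stands, and it limits the point to a conditional one of modest size.

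Some stronger readings are tempting but not supported:

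- *The type I error is definitely below 5%.* That needs a prognostic stratum. At gallstone risk ratios of 1–2 the crude test runs at 0.048–0.051.
- *The excess variance equals the same percentage of extra patients.* The variance ratio is computed under no effect. At 11.5% control risk it implies 1/0.958, or 4% extra, at risk ratio 3 and 1/0.870, or 15%, at 6. The patient equivalent of the power gain is [(z₂ + 1.96)/(z₁ + 1.96)]², where z₁ and z₂ are the normal quantiles of the two powers. For 0.812 → 0.820 this is about 2%, and for 0.820 → 0.844 about 7%, roughly half as much.
- *A chi-squared analysis cannot be combined over imputed data sets.* The plan pairs the test with a risk ratio and requires confidence intervals. A crude log risk ratio has a standard error and can be pooled by Rubin's rules.
- *Every secondary chi-squared test loses precision in the same way.* Newly formed gallstones are analysed only in patients without gallstones at baseline, so that stratum is constant there.
- *The editors' clause alters the primary test.* The chi-squared p value is the same whichever ratio is printed. What changes is the reported measure: at 10% v 5% the risk ratio is 0.50 and the odds ratio (0.05/0.95)/(0.10/0.90) = 0.47.

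**Conclusion.** The design stratifies and the primary analysis does not. Conditional on baseline gallstones being prognostic, the planned p value and interval are mildly conservative. Over assumed gallstone risk ratios of 3–6, alpha is about 0.046–0.031, the risk-ratio interval about 1–6% too wide and the power loss about 0.4–3.4 points. The far end is a strong assumption: risk ratio 6 at a 15% control rate means risks of 7.5% and 45%. At risk ratios of 1–2 almost nothing is lost.

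These figures rest on the assumed stratum risks, on an N set for 80% power, and on surgery type not being prognostic. The interval-width result applies to the risk ratio. An adjusted odds ratio is a conditional quantity whose interval need not be narrower, although its test still gains power.

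Severity is low to moderate: a free gain in efficiency, with no threat to validity.

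**What to change.** Before unblinding, amend the SAP as follows.

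1. Make the primary analysis a CMH test with the Mantel-Haenszel risk ratio and 95% confidence interval, stratified by baseline gallstones and type of surgery. A modified Poisson model with arm and both factors is an alternative. It targets a similar risk ratio, though it is not identical in weighting or variance, and is convenient if outcomes are imputed. Name one as primary.
2. Use the strata as randomised. The Discussion says that a minority of patients had an operation other than the one stratified on, and that surgery type became a stratification factor only when sleeve gastrectomy was added.
3. Keep the crude chi-squared test as a sensitivity analysis.
4. Apply the same approach to cholecystectomy and to presence of gallstones/sludge at 24 months. For newly formed gallstones, stratify by surgery type only.
5. Keep the risk ratio as the primary effect measure whatever editors prefer; any odds ratio is reported in addition.

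The cost is SAP wording. Both factors were needed to randomise each patient, so no new data are required. If the strata turn out not to be prognostic, adjustment costs essentially nothing: at gallstone risk ratio 1 the simulated powers of the two tests agree to within 0.1 point at control rates of 11.5% and 15%.
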